Implementation will be augmented in the following ways. First, we will establish a broad network of core "faculty advocates" in the intervention teams. Advocates will act as role models and provide direct verbal instruction to their colleagues on the team. We will ask the Patient Care Managers (or equivalents) on intervention teams to enlist the support of staff members who are willing to champion the intervention. Second, advocates will receive initial training about the intervention etiquette from research staff. Third, researchers will provide consultation to advocates to support them in the training, implementation, and uptake goals. Finally, we will use email as a delivery channel to inform advocates of the latest research results and to offer suggestions for reinforcement throughout the duration of the study. The responsibility for implementation of the intervention therefore is shared by researchers and staff-participants in GIM. We anticipate that these combined initiatives will promote increased buy-in and uptake among front line staff-participants in the GIM experimental teams.

In each intervention CTT we expect that thirty minutes will be required to explain the intervention to professional leaders and to field questions. We expect it will take ten minutes of discussion by each of the professional leaders with their trainee or reporting colleagues in each profession. We expect that the time cost of reinforcement will be fleeting, and might occur two or three times per week, at such times as regular rounds or meetings within professions, in interprofessional team meetings, in individual supervision and education meetings, and in opportunistic conversations.

The intervention will run approximately eight weeks in the intervention CTTs. In this time it will expose two rotations of staff and resident physicians and the other health professional staff with whom they work on the teams to the communication and collaboration script. At each hospital site, staff and patient outcomes related to each of the two intervention and control health care teams will be compared.

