#### Covariates

Model-based estimates of intervention effects on the outcomes of readmission, length of stay, use of optimal drug therapy, patient satisfaction, and use of paging devices will employ patient-level and team-level covariates. Patient-related factors to be controlled will be patients' age and gender.

Other covariates will be measures of hospital health care processes hypothesized to be related either to outcome measures or to intervention uptake. The intervention's focal concern is the improvement of interprofessional performance of GIM teaching teams. Therefore, we propose to use the following constructs as structural indicators of functional team processes of care:

• *Ward-based assignment of medical, nursing, and allied health professional staff*. 'Ward basing' refers to hospital practices specifying the deployment of healthcare staff members to a single physical ward location. This arrangement is in contrast to assignments that have staff members working among different medical teams or nursing units as they treat patients. For example, if nurses and nursing units are fixed to physical ward locations, then medical team and professional health staff members could be assigned to patients in such a way that they are required to work with members of several different nursing units. If so, they are said to 'cross teams or units.' On the other hand, if medical teams are fixed to physical ward locations, then it is possible that nurses and professional health staff could be required to work among multiple different medical teams. It is also possible that both medical teams and nursing units are given fixed assignments to single ward locations and professional health staff are assigned to work across multiple combinations of medical teams and nursing units. All of these configurations create variation in the degree to which GIM staff are consolidated to work in one physical location.

Work assignments that see GIM staff consistently – and as a matter of hospital policy – working in multiple physical locations, where work colleagues are more likely than not to be unfamiliar, might have negative impacts on achievement of effective interprofessional collaboration and patient outcomes. An indicator variable will be developed to code whether clinical teaching teams are organized to consolidate interprofessional teams and team members to a single physical ward location.

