• *Team-dedicated discharge planner/coordinator*. GIM divisions in some TAHSN hospital sites utilize identified individuals in discharge planning roles as Discharge Planners or Discharge Coordinators. In other sites the discharge coordination function is a responsibility of licensed social workers. We suggest both that patient outcomes with respect to readmission and length of stay, and increased team collaboration and coordination, are influenced positively when the role of discharge planning is performed by an individual with dedicated, team-focused discharge responsibilities (e.g., a registered nurse) instead of an individual with discipline-specific responsibilities (e.g., a social worker). Measured at the level of the clinical teaching team, this construct will be a binary coding of whether the team employs a full-time discharge planner (typically a registered nurse), a social worker with additional responsibilities of coordinating discharge planning, or another individual.

• *Length of regularly scheduled meeting time for interdisciplinary rounds, per team*. We define an 'interdisciplinary round' as a patient-focused meeting that occurs at least one day per week (Monday to Friday), every week, where regular attendance is expected by a team resident physician and leaders of two other clinical professions, nursing and allied health professional staff. The variable will be measured at the level of the clinical teaching team, operationalized as average (mean) meeting hours per week during the time the intervention is implemented at the hospital site.

• *Nursing staff characteristics*. Measures will be developed to adjust for team-level variation in nurse staffing. It is expected that hospital administrative data will be available to enable development of measures of nursing staff characteristics such as: (1) the mean of the daily proportion of registered nurses in a team's staffing mix while the intervention was in progress, or (2) the mean of the daily proportion of nurses with baccalaureate degrees who worked on a team while the intervention was in progress, and (3) the proportion of a team's nursing hours performed by registered nurses per unit of time, or (4) the proportion of a team's nursing hours performed by baccalaureate-prepared nurses per unit of time.

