• *Nursing workload measures*. Data are expected to be available to measure team-level variation in nursing workload. Measures will be continuous variables and could include: (1) the patient-to-nurse ratio per unit of time during the intervention period, per team; (2) the mean number of hours of nursing care worked on a team, per patient-day during the intervention period; or (3) nurses' acuity-adjusted patient load per unit of time during the intervention, per team.

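### Several team-level adjustment covariates are measured during the intervention, after allocation, so the adjusted effect estimates may be distorted and may no longer be the total effect

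*Protocol article*

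**What the plan says.** The Covariates section states that the model-based estimates for readmission, length of stay, optimal drug therapy, patient satisfaction and paging "will employ patient-level and team-level covariates". The patient-level ones are age and gender. The others are described as "measures of hospital health care processes hypothesized to be related either to outcome measures or to intervention uptake", and the section calls them "structural indicators of functional team processes of care".

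Five team-level constructs follow:

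- **Ward-based assignment of staff:** an organizational indicator with no measurement period stated.
- **Dedicated discharge planner:** a coding of who does the job, with no measurement period stated.
- **Interdisciplinary-round time:** "operationalized as average (mean) meeting hours per week during the time the intervention is implemented at the hospital site".
- **Nursing staff characteristics:** four options. Option 1 concerns the registered-nurse share of the "staffing mix while the intervention was in progress", and option 2 uses the same period for baccalaureate nurses. Options 3 and 4 are proportions of nursing hours per unit of time, not tied to the intervention.
- **Nursing workload:** three options, all taken in the intervention period: patient-to-nurse ratio, acuity-adjusted load, and "the mean number of hours of nursing care worked on a team, per patient-day during the intervention period".

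No baseline value is specified for any of them. Under Sequence generation, each site's four teams are allocated before its intervention period. Statistical methods promises an intention-to-treat comparison. The Readmission paragraph gives the population-level intervention effect as the primary aim, to be estimated with generalized estimating equations.

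**The concern.** Randomization protects a comparison adjusted for variables fixed before allocation. It does not protect one adjusted for variables that the allocated condition may have changed. If such a variable carries part of the effect, adjustment takes that part out. If it also shares an unmeasured cause with the outcome, adjustment opens a non-randomized path whose bias can go either way.

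Hypotheses 1, 3, 5, 6 and 7 (readmission, length of stay, satisfaction, paging, drug therapy) all ask for the overall difference between intervention and control teams. The adjusted models cover those same five outcomes, so the interpretation of the primary model-based estimate is at stake. The timing is written into the article itself, so this is not a detail left to an analysis plan.

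**Working it through.** **1. Which covariates are affected.**

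| Covariate | Timing in the article | Can the intervention plausibly move it? |
|---|---|---|
| Ward-basing | none stated | outside this point |
| Discharge planner | none stated | outside this point |
| Round hours | during intervention | possible but weak |
| Nurse mix, options 1–2 | during intervention | weak |
| Nurse mix, options 3–4 | per unit of time only | not clearly within this point |
| Workload, options 1–3 | during intervention | credible |

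**2. Why workload is the strongest case.** Let H be a team's nursing hours, N its number of patients and L their mean length of stay. Nursing hours per patient-day is then approximately H / (N × L). Hypothesis 3 predicts a smaller L in intervention teams. If L falls by a fraction s while H and N stay the same, the ratio becomes H / (N × L × (1 − s)), which is the old value divided by (1 − s). The covariate then differs between arms because of the intervention. In the length-of-stay model it also carries information about the outcome itself. The patient-to-nurse ratio depends on census in the same way. If freed beds refill so that N × L is unchanged, or if nursing hours follow census, the ratio need not move. The link is credible but not automatic.

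**3. Why round hours are weaker.** Reinforcement is given "at such times as regular rounds or meetings within professions, in interprofessional team meetings", so a pathway through meetings exists. But the covariate counts regularly scheduled time, while the Background says that the intervention is aimed at encounters outside structured meetings.

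**4. The plan's own power figures.** Inputs from Sample size: 20 teams (10 per arm), 200 patients per team, intracluster correlation 0.01, p < 0.05 (taken as two-sided).

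- Design effect = 1 + (200 − 1) × 0.01 = 2.99.
- Effective number per arm = 10 × 200 / 2.99 = 668.9.
- 10% versus 5%: null standard error √(2 × 0.075 × 0.925 / 668.9) = 0.01440; alternative √((0.09 + 0.0475) / 668.9) = 0.01434; z = (0.05 − 1.96 × 0.01440) / 0.01434 = 1.52; power 93.6%, against 93% stated.
- 5% versus 2.5%: the same steps give 67.3%, against 67% stated.

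Both figures reproduce. They refer to the total effect with no covariate adjustment and are not in dispute.

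**5. Illustration of the mechanism.** In a linear model, if a share q of the total effect runs through the adjusted covariate and nothing else confounds the two, the adjusted estimate is 5 × (1 − q) points. The documents give no value for q.

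- q = 0: 5.0 points, no bias.
- q = 20%: 5 × 0.8 = 4.0 points.
- q = 40%: 5 × 0.6 = 3.0 points.
- q = −20% (the covariate works against the benefit): 5 × 1.2 = 6.0 points, an overstatement.

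A simulation of 20 teams in five sites with a true effect of −5.0 points agrees with the formula. Adjusted estimates were about −4.5, −4.0, −3.5 and −2.5 at shares of 10, 20, 30 and 50%. The unadjusted estimate stayed near −5.0, and at a share of zero the adjusted one was unbiased. The simulation assumed that the intervention shifts the covariate by 2 standard deviations, a deliberately large value, so its power results say nothing about this trial.

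**The case against.** The other side has several good points.

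- **Weak mediators.** Reinforcement is expected to take little time and uses existing meetings, and Potential harms says that care processes are not greatly changed. Nothing suggests that an eight-week communication script alters the share of registered or baccalaureate nurses. At some sites nurses serve both arms, which limits any between-arm difference there. This stands, and it is why round hours and nurse mix rank below workload.
- **The uptake wording.** A reader might take "hypothesized to be related either to outcome measures or to intervention uptake" as an admission that the covariates are consequences of the intervention. It is not. The ward-basing rationale runs from structure to collaboration and outcomes, so the phrase more naturally describes determinants of uptake. The concern rests on when the variables are measured.
- **An unadjusted test exists.** The cluster-adjusted chi-square for readmission names no covariates, so the total effect on the primary outcome is also tested. This stands, but the article still commits the model-based estimate of that outcome to the covariates.
- **Choice among nursing measures.** A reader might infer that one option will be picked after results are seen. The article lists candidates subject to data availability and does not say when the choice is made. Final selection is commonly left to an analysis plan, and group assignment is expected to be masked from the statistician for readmission, length of stay and drug therapy.

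**Conclusion.** The point holds in a limited form. Followed as written, the plan conditions its model-based effects on variables measured after allocation. That sits badly with its intention-to-treat comparison and its aim of estimating a population-level effect. Workload is the serious case; round hours and nurse-mix options 1–2 are lesser ones.

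Two stronger readings are not supported. The first is that adjustment necessarily removes part of the effect. Bias arises only if a covariate is affected by the intervention and is related to the outcome, the documents do not show that this happens, and the direction is not fixed. The second is that power falls from 93% to roughly 50–77%. Those values come from putting the 3.0- and 4.0-point illustrations into the unadjusted power formula. They rest on an assumed share, keep the unadjusted standard error for an adjusted estimate, and do not describe the chi-square test.

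The size of any bias cannot be derived from the documents. The 3.0–4.0 points remaining of 5 are an illustration only.

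**What to change.** Define round hours, the nurse-mix measures and the workload measures over a fixed window that ends before each site's allocation, for example the preceding eight weeks, using the same sources. Alternatively, leave them out of the main effect models. Either way, keep the during-intervention values for describing care processes or for an analysis labelled exploratory.

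Teams are allocated site by site, so the window can be set separately for each site. The nursing data are already expected from hospital administrative records. The source for round hours is not stated, but the standing schedule could be noted before allocation.

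The cost is a small additional data extract with no patient contact. Baseline values may also correlate slightly less with outcome than concurrent ones, which would give up a little precision.

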#### Qualitative data

Observational notes and interviews will be analyzed with a thematic inductive approach, whereby meanings emerge from the data and are grouped into key themes and sub-themes [38]. The research team will discuss and negotiate the emerging analyses to help improve conceptual understanding, and reach agreement on interpretation. The data will be analyzed from the perspectives of intervention impact and staff behavioural and perceptual changes over time. Interaction frequencies will be analyzed to examine intervention uptake.

#### Potential benefits

The SCRIPT intervention was developed with a goal of increasing interprofessional collaborative communication. It is expected that strong collaborative communication is a factor in achieving (i) better patient health outcomes in shorter times, (ii) higher reported patient satisfaction with the experience in the GIM department, and (iii) improvements to the hospital work environment gained through perceptions of increased commitment to collaboration and fewer interruptive communications.

If analyses find that use of evidence-based prescription drug therapy is more likely or more abundant among intervention teams than control teams, then a range of benefits are possible. For example, satisfactory ability to manage a patient's disease could be increased, complications and length of stay could be reduced, and discharge could be made more rapidly. Moreover, if there is a general causal relationship between sub-optimal prescription drug therapy and subsequent unplanned readmission to hospital, investigations into prescription drug use could inform remedial goals of reducing drug-related unplanned readmissions.

#### Potential harms

Potential for harms is minimal. The trial poses low risk because it requires no contact between patients and the research team, and because the intervention does not impose major changes on health care processes. There is no expectation that participants from whom data are collected for any of the quantitative outcome measures will face any harm.

A privacy-related concern surrounding use of data relating to prescription drug therapy involves our pursuit of a dataset that could be used to identify GIM teams where patients' prescription drug therapy was shown to be sub-optimal or not regularly in accord with evidence-based best practices. We recognize that it is necessary to protect confidentiality of GIM members whose roles give them responsibility for influencing segments of GIM patients' prescription drug therapy. Data and analyses used in these investigations will be stored and disseminated with great sensitivity.

At the same time, given the evidence base that now exists to help guide appropriate therapeutic use of prescription drugs, an investigation of prescription drug therapy as an outcome measure in an intervention study is a highly important and legitimate research endeavour.

Confidentiality of individual, patient-level records relating to hospital readmissions, lengths of stay, and prescription drug therapy is governed by policies and procedures of the Institute for Clinical Evaluative Sciences. ICES policies are both strict and effective. These data records can not be removed on any storage or transport medium from the physical ICES premises. ICES data facilities employ stand-alone data servers that are not connected to the Internet.

## Discussion

Despite continuing international interest in improving interprofessional collaboration and service delivery in health care [2,3], the evidence base for interventions is inconclusive [6,8]. This cluster randomized controlled trial is the first study that will explicitly design and rigorously evaluate a front-line intervention on interprofessional collaborative communication to support patient-centred care.

Previous research has indicated that well-coordinated interprofessional collaboration is difficult to achieve in fast-paced acute care hospital environments [39,40]. Given this situation, the design of an effective intervention requires care and attention to important contextual factors. To ensure the intervention will be both sufficiently sensitive and robust to operate within such environments, as outlined above, we undertook a series of preliminary qualitative observations within the study sites.

An important finding from our qualitative data is that opportunities for interprofessional collaborative communication occur during informal, unplanned interactions, outside of formal structured meetings. These opportunistic interactions can be highly consequential: they are initiated by professionals many times during a working day, usually to obtain information from another professional who is sharing responsibility for the same patient, and/or to impart information to him or her about the patient. Analysis has shown that three core elements of communication are typically absent from such encounters: named self-introduction and description of role with respect to the patient under discussion; sharing of planned activities for the patient; and elicitation of the counterpart's point of view. We drew upon these findings to design an intervention for creating a culture of interprofessional communication where the fundamentals of collaboration are a routine and normalized part of opportunistic, informal encounters.

Our outcome measures are well-suited to measuring the intervention's impact, because they are measures with large, motivated, and interested constituencies: front line hospital staff, hospital managers, and patients. Two outcome measures in particular – paging frequency and continuity of pre- and post-hospital drug therapy – can help investigate novel hypotheses bearing on the complexities and consequences of interprofessional collaborative communication. They have excellent potential to redress existing clinical and community problems in interprofessional team communication.

## Abbreviations

CMSS – Collaboration among Medical Staff Subscale

CPSO – College of Physicians and Surgeons of Ontario

CTT – Clinical teaching team

DAD – Discharge Abstract Database

GIM – General internal medicine

ICES – Institute for Clinical Evaluative Sciences

IECPCP – Interprofessional education for collaborative patient-centred practice

LOS – Length of stay

ODB – Ontario Drug Benefit

OHA – Ontario Hospital Association

PASS – Power Analysis and Sample Size

PGY*n *– Post-graduate year *n*

RCT – Randomized controlled trial

SCRIPT – Structuring Communication Relationships for Interprofessional Teamwork

TAHSN – Toronto Academic Health Sciences Network

UK – United Kingdom
